#### Finalising the long list

Extracted outcomes/domains that were added to the long list will initially be mapped, where possible, onto domains identified in the rheuCOS-SDMi. Outcomes that do not align with existing rheuCOS-SDMi domains will be reviewed and grouped into further higher-order outcome domains (guided by the executive steering group and the PPAG) to be presented separately during subsequent stages. The process of grouping outcomes will be guided by existing frameworks, including the Outcome Measures in Rheumatoid Arthritis Clinical Trials (OMERACT) filter 2.1^44^ and the COMET outcome taxonomy,^45^ to create a long list of candidate outcome domains. Descriptions of outcome domains will draw on consensus-definitions agreed in the rheuCOS-SDMi or will be grounded in systematic review evidence, wherever possible. The long list will undergo at least two rounds of review by the executive group and the PPAG and iterative refinement. Members will be asked to independently review a draft of the long list to assess its overall comprehensibility and its comprehensiveness, structure and relevance to the new context. Written comments will be collected and separate meetings with executive group and PPAG members will also be organised to provide an opportunity to discuss and further elaborate on their feedback. The study delivery team ([name], [name], [name], CH, MS, SL, TN) will collate and synthesise all feedback, and revisions will be made in response to identified issues. Attention will be given to refining wording (eg, outcome domain labels and explanations), resolving ambiguities, and ensuring that outcome domains are understandable and accessible for all interest holder groups. Further rounds of comments and revisions will be sought as appropriate to ensure all feedback has been appropriately addressed until a final long list is agreed to be taken forward to step 2.

### Step 2: Rating of the essentiality of outcome domains

A two-round international online Delphi will be used to agree on a shorter list of outcomes and outcome domains.

#### Delphi survey development

All outcome domains will be operationalised into an online Delphi questionnaire. Draft surveys will be piloted by members of the PPAG and selected individuals from the executive group and iteratively refined. This involves asking individuals to complete the full survey independently and provide written feedback to the study delivery team about the usability and face validity (ie, clarity and relevance) of the survey instructions and response scales, with identified issues addressed where appropriate.

The questionnaires will be hosted online using appropriate software (eg, REDCap). Questionnaires will be developed in English. The executive group considered multi-lingual COS development; however, a single language option was preferred to retain conceptual consistency during the survey development and because of concerns about feasibility within the resources available for the study.

#### Data collection

Participants will be invited to complete two consecutive rounds of the survey. In Round 1, participants are asked to provide sociodemographic details to determine the relevant panel group. During both rounds, participants will be asked to rate the importance of assessing each outcome domain using a Likert scale based on the Grading of Recommendations, Assessment, Development and Evaluations (GRADE) scale.^46^ This means scoring will be undertaken using a 9-point Likert scale with 1–3 labelled ‘not essential’, 4–6 labelled ‘important but not essential’ and 7–9 labelled ‘absolutely essential’.^46^ There will also be an ‘Unable to answer’ option for each question with the ability for the participant to enter free text to explain why they were not able to score the item. A single ‘free text’ response option at the end of the survey will be included to allow participants to suggest any additional domains. Participants will be informed that they should not base their responses to the survey on whether a validated measure is already available for a particular outcome domain. Outcome domains will be worded neutrally, in a way that can be interpreted bidirectionally without influence on the participant, that is, ‘patient trust’ as opposed to ‘more patient trust’ or ‘less patient trust’.

New potential outcome domains, identified by at least 10% of respondents through the free text response, will be included in subsequent Delphi rounds if deemed within scope. Only participants who complete Round 1 will be invited to Round 2. All questions will be mandatory to minimise missing data. Questions presented in Round 2 will be accompanied by feedback from Round 1 responses and participants will be asked to reconsider their response in light of this feedback. Feedback will consist of the average score for each question for each participant panel (ie, median score per outcome domain/question for each sub-group) and the individual participant’s own previous rating. All items will be retained in full between survey rounds 1 and 2. All items still retained after Round 2 of the Delphi survey will be taken forward to the consensus meeting where the final COS will be agreed.^32^ A third Delphi round will be considered if necessary.

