#### Participant recruitment

The Delphi process will be undertaken inclusive of all interest holders relevant to this project. Participants will be recruited through adverts disseminated by established international SDM societies and OMERACT networks. Those approached will not be offered any financial incentive to participate. Participants will be purposively approached to ensure variation in key characteristics including sex, geographical location, ethnicity, age, healthcare experience or professional/clinical expertise (depending on the interest holder group). Participant characteristics will be reported using the PROGRESS+framework.^47^ Round 1 Delphi survey participants will be asked to confidentially provide their email address which will be used to facilitate recruitment for Round 2 Delphi survey. A direct email will be sent which will include an embedded link to the second round. A minimum of 150 participants per panel will be sought, in line with previous COS development studies.^32^ There will be no maximum sample size, and a weighted percentage will be considered should participant numbers be uneven across the different panels (eg patient/carer vs professionals).^32^

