#### Analysis

Participant data will be separated into at least two Delphi panels depending on which interest holder group they represent. As a minimum, participants may be divided into patients, carers and family members (panel 1) and professionals including clinicians and SDM researchers (panel 2), to be able to assess differences in priorities and to avoid overrepresentation of a single group.

Participant response scores for the Delphi process will be analysed using descriptive statistics, adhering to the GRADE criteria.^46^ Analyses will be conducted separately for each panel and average scores calculated (ie, the median score of each panel per outcome domain/question). Results for each panel will be presented visually as feedback in Delphi Round 2. Final Delphi survey scores will again be subject to descriptive analyses with any changes in participant scores between rounds examined.

Response statistics and participant characteristics will be examined using descriptive statistics and presented in tabulated format by panel group. Attrition between Delphi survey rounds will be examined for potential bias in the different participant panels, comparing scores between participants who have completed only one Delphi survey round versus participants who have completed both Delphi survey rounds.

All analyses will be conducted with the help of a statistical software package (eg, Stata).

Recommended definitions of consensus will be followed during all rounds of the Delphi survey (see box 4).^36^

Box 4Consensus criteriaConsensus IN is defined as >70% of the total participants rating the outcome domain as 7–9 (‘absolutely essential’) and<15% rating the outcome domain as 1–3 (‘not essential’). This means the outcome domain will be taken forward to the consensus process.Consensus OUT is defined as >70% of participants rating the outcome domain as 1–3 (‘not essential’) and<15% rating the outcome domain as 7–9 (‘absolutely essential’). This means the outcome domain will not be taken forward to the consensus meeting.All other combinations of response results are defined as NO CONSENSUS.

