### Step 3: Consensus on the final COS

Multiple international online consensus meetings will be conducted to discuss the results of the Delphi and, informed by the Delphi, to agree on a final COS-SDMi. This qualitative element provides an opportunity for experts in SDM to discuss and contextualise the quantitative Delphi findings. This approach also enables exploration of differing perspectives across interest holder groups, supports clarification and refinement of outcome domains, and facilitates transparent decision-making regarding inclusion, exclusion, or consolidation of outcomes.

The number of meetings will be determined in discussion with the executive group, considering the geographic representations and involvement of diverse interest holders. For example, it is anticipated that three meetings will be held to accommodate time zones in North and Latin America, Europe and Africa, Australia and Asia.

Recruitment for the consensus meetings will be targeted and facilitated through international SDM societies (eg, ISDM) and OMERACT networks, and key informant approaches. It is anticipated that no more than 25 participants, with fair representation of the interest holder groups listed above, will participate in each consensus meeting. A secure video conference platform will be used to host the meetings.

At each meeting, Delphi results will be presented by an independent chairperson with an understanding of SDM interventions. The Chair will lead structured discussions about the proposed inclusion/exclusion of domains from the COS, based on the consensus definitions. This will include discussions about combining outcomes depending on similarity. Any divergence in consensus between the two panel groups will be discussed. Interactive, anonymous voting will be used to gain consensus on proposed domains that achieve ‘NO CONSENSUS’ after the Delphi rounds. Those domains achieving ‘IN’ or ‘OUT’ status after the Delphi will simply be presented as such, and voting on these will only take place if there is sufficient objection to the status of these domains. Should a large number of outcome domains achieve ‘IN’ status after the Delphi, discussions will explore consolidating them into higher-order outcome domains.

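### The rating labels for 1–3 and 4–6 overlap in wording, so middle views may be scored 1–3 and move domains near a Box 4 cut-off, most seriously towards OUT

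*Protocol article*

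**What the plan says.** Under Step 2, Data collection, respondents in both rounds are asked to "rate the importance of assessing each outcome domain" on a 9-point scale. Its bands are "1–3 labelled ‘not essential’, 4–6 labelled ‘important but not essential’ and 7–9 labelled ‘absolutely essential".

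Box 4 (Step 2, Analysis) turns these scores into a status:

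- **IN** needs more than 70% scoring 7–9 and fewer than 15% scoring 1–3.
- **OUT** mirrors this: "Consensus OUT is defined as >70% of participants rating the outcome domain as 1–3 (‘not essential", with fewer than 15% scoring 7–9. An OUT domain does not go on to the consensus meeting.
- Every other pattern is NO CONSENSUS.

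Two other provisions bear on the point. Under Delphi survey development, pilot users comment on the "face validity (ie, clarity and relevance) of the survey instructions and response scales, with identified issues addressed where appropriate". Under Step 3, "Interactive, anonymous voting will be used to gain consensus on proposed domains that achieve ‘NO CONSENSUS’ after the Delphi rounds". Domains that are IN or OUT are presented as such and are voted on only if there is enough objection.

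**The concern.** The lowest two labels are not mutually exclusive as worded. A domain that is important but not essential is also, in plain English, not essential. The word that would separate the bands is 'important', but the lowest label never says 'not important'. The question asks about importance, while the lowest and highest labels are only about essentiality.

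The overlap runs one way. A respondent with a middle view is described by both lower labels. A respondent who thinks a domain unimportant is described only by the lowest. The plausible error is therefore middle views recorded as 1–3.

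Box 4 relies on that boundary. A 4–6 score neither blocks IN nor supports OUT; a 1–3 score does both. If some middle views are recorded as 1–3, a domain could lose IN or be classed OUT because of how a label was read rather than what respondents think of the domain.

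**Working it through.** The plan gives no figure on this point to reproduce. The check applies the Box 4 rule to assumed rating distributions.

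**Inputs**
- From Box 4: IN if the 7–9 share is above 70% and the 1–3 share is below 15%; OUT if the 1–3 share is above 70% and the 7–9 share is below 15%.
- From Participant recruitment: "A minimum of 150 participants per panel will be sought". The figure of 150 is used below only to turn percentages into counts.
- Assumed: the distributions. L, M and H are the shares in 1–3, 4–6 and 7–9 if every respondent reads the labels as intended.
- Assumed: m, the fraction of middle raters who score 1–3 instead.

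**Formula.** The recorded 1–3 share is L + m × M, and H does not change.
- IN is lost when L + m × M reaches 15%, so m = (15 − L)/M.
- OUT is reached when L + m × M exceeds 70% (with H below 15%), so m must be above (70 − L)/M.

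**From IN to NO CONSENSUS**

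| 1–3 / 4–6 / 7–9 (%) | Calculation | m at which IN is lost |
|---|---|---|
| 12 / 13 / 75 | 3/13 | about 23% |
| 10 / 15 / 75 | 5/15 | about 33% |
| 5 / 23 / 72 | 10/23 | about 43% |
| 5 / 20 / 75 | 10/20 | 50% |
| 5 / 15 / 80 | 10/15 | about 67% |
| 2 / 12 / 86 | 2 + 12 = 14, below 15 | never |

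The 15% limit can matter only when the 7–9 share is above 70% and at most 85%. With 150 raters, 70% is 105, so IN needs at least 106 scoring 7–9. Also, 15% is 22.5, so 23 or more scores of 1–3 break IN. That is possible only with at most 150 − 23 = 127 scoring 7–9.

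**From NO CONSENSUS to OUT**

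| 1–3 / 4–6 / 7–9 (%) | Calculation | m above which the domain is OUT |
|---|---|---|
| 65 / 25 / 10 | 5/25 | 20% |
| 55 / 35 / 10 | 15/35 | about 43% |
| 40 / 50 / 10 | 30/50 | 60% |

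Among the examples that change status, about 20% to 67% of middle raters must score 1–3.

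**The case against.** The strongest reply is that nothing in the decision rule is ambiguous. Box 4 is written in scores, with labels only in brackets. The bands are separate and cover 1 to 9, so any set of scores gives exactly one status. This stands. A reader might infer that the 1–3 share itself is ill defined, and the document does not support that.

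Second, the labels sit on an ordered scale, and the middle view has a label of its own next to the lowest one. Most respondents will probably find it. This limits mis-sorting but does not rule it out, and the document gives no information on how often it would happen.

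Third, the pilot asks about the clarity of the response scales before launch. It may catch the problem, but it does not guarantee a change.

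Fourth, the consequences are mostly recoverable. A domain that loses IN goes to an anonymous vote. That stands for IN. It protects less against a wrongful OUT, where a vote depends on enough objection being raised.

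Three stronger readings should be resisted:
- With 300 raters, 44 scores of 1–3 (14.7%) keep IN and 45 (15.0%) lose it. That is the edge of any 15% cut-off and would exist with perfect labels, so it does not measure the overlap.
- If 80% regard a domain as not essential, it misses OUT once one in eight of them scores 4–6 (0.70/0.80 = 87.5%). But a domain that some raters find important should miss OUT, so here the bands work as intended.
- Patients and professionals might read the labels differently. This is possible, but nothing in the document shows it.

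**Conclusion.** The point holds as a minor weakness of the rating instrument, not as an error in the consensus rule. The two lower labels overlap in wording, and Box 4 attaches different consequences to the two bands.

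The effect is limited to domains near a cut-off and needs a substantial share of middle raters to score 1–3: about 23% for 12/13/75% to lose IN, and just above 20% for 65/25/10% to become OUT. These figures rest on assumed distributions and an assumed mis-sorting fraction. The document supplies neither, so they show what could happen and not what is likely.

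A wrongful OUT matters most, because the domain is then dropped by default. It is also a demanding condition: over 70% must score 1–3 and under 15% must score 7–9.

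**What to change.** Before Round 1 opens:

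1. Reword the 1–3 label so that it excludes the 4–6 meaning, for example 'not important'. The three labels then form exclusive, ordered steps.
2. Use the same label for 1–3 in both places where Box 4 names it.
3. In the planned pilot, ask specifically which band a respondent would use for a domain that is important but not essential.

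The cost is a wording change in the survey and Box 4 and one extra pilot question. The bands, thresholds, sample size and analysis do not change. Timing matters: a label changed after Round 1 would make the planned comparison of scores between rounds harder to interpret.

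### The 10% free-text rule for new Delphi domains names no panel denominator, and a domain it admits can gain IN or OUT status on one rating given without feedback

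*Protocol article*

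**What the plan says.** All the provisions are in the protocol article.

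- **How a domain is raised.** Step 2, Data collection: "A single ‘free text’ response option at the end of the survey will be included to allow participants to suggest any additional domains".
- **How it gets in.** Same section: "New potential outcome domains, identified by at least 10% of respondents through the free text response, will be included in subsequent Delphi rounds", if judged within scope. No panel is mentioned.
- **Rounds.** "Participants will be invited to complete two consecutive rounds of the survey". Also: "A third Delphi round will be considered if necessary". No trigger is given, and the third round is not linked to new domains.
- **Feedback.** "Questions presented in Round 2 will be accompanied by feedback from Round 1 responses". It consists of each panel's median and the participant's own earlier rating.
- **Sample.** Participant recruitment: "A minimum of 150 participants per panel will be sought", with no upper limit. The abstract gives a minimum of 150 participants without saying per panel. A weighted percentage is to be considered if panel sizes are uneven, but this is not tied to the 10% rule.
- **Panels.** Analysis sets up at least two (patients, carers and family; professionals), partly so that no one group dominates.
- **Status.** Box 4 defines IN as more than 70% rating 7–9 and fewer than 15% rating 1–3. OUT is the mirror image, and everything else is NO CONSENSUS. The criteria apply in all rounds.
- **Voting.** In Step 3, NO CONSENSUS domains are voted on. IN and OUT domains are only presented, and are voted on only if there is enough objection.

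**The concern.** The Rationale says it is unclear whether domains drawn from rheumatology are comprehensive in other settings. The Round 1 free-text box is the one described point at which the wide international sample can say what is missing. Step 3, as described, discusses and combines proposed domains but gives no route for adding one.

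Two features of the rule look wrong.

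1. The threshold has no stated denominator. If it is pooled, a domain that matters to one panel only is diluted by the other panel's silence. The smaller panel is diluted most.
2. A domain that enters in Round 2 has no Round 1 score. It misses the feedback and reconsideration every other domain receives, yet it is classified by the same criteria and can reach the final stage with its status already settled.

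At stake are which domains enter the consensus process and how firmly the status of a late entrant is established.

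**Working it through.** **Inputs.** From the article: a 10% threshold, at least two panels, two planned rounds, and a minimum of 150 per panel (Participant recruitment) or 150 participants (abstract). The article gives no derivation of the 10%, so there is no figure to reproduce. The share of respondents who would name a missing domain is not given either. It is an assumption below, shown over a range.

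**Step 1: share needed within one panel under a pooled rule.** If only one panel raises the domain and that panel is a fraction w of all respondents, the share needed is 0.10 / w.

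| Panel / total | w | Mentions needed | Share of that panel |
|---|---|---|---|
| 150 / 300 | 1/2 | 30 | 30/150 = 20% |
| 75 / 150 | 1/2 | 15 | 15/75 = 20% |
| 150 / 450 | 1/3 | 45 | 45/150 = 30% |
| 150 / 600 | 1/4 | 60 | 60/150 = 40% |

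The last two splits are illustrative. If the weighting under consideration gave two panels equal weight, the condition would be (p + 0)/2 ≥ 0.10, so p ≥ 20%. That removes the extra penalty on the smaller panel but not the doubling.

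**Step 2: chance that a domain raised only by patients is admitted.** Exact binomial: P(X ≥ r), X ~ Bin(n patients, p). The pooled rule has r = 10% of the total; the within-panel rule has r = 10% of n, rounded up. Respondents are taken as independent with a common p.

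| p among patients | Pooled, 150 of 300 (r = 30) | Within panel, 150 (r = 15) | Pooled, 75 of 150 (r = 15) | Within panel, 75 (r = 8) |
|---|---|---|---|---|
| 10% | 0.0002 | 0.54 | 0.007 | 0.48 |
| 15% | 0.06 | 0.97 | 0.15 | 0.89 |
| 20% | 0.53 | >0.99 | 0.55 | 0.99 |
| 25% | 0.94 | >0.99 | 0.87 | >0.99 |

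**Step 3: a domain raised equally by both panels, 300 in total.** The pooled chance is P(X ≥ 30), X ~ Bin(300, p). The either-panel chance is 1 − (1 − q)², where q = P(X ≥ 15), X ~ Bin(150, p).

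| p | Pooled | q | Either panel |
|---|---|---|---|
| 5% | 0.0003 | 0.0085 | 0.017 |
| 8% | 0.12 | 0.22 | 0.39 |
| 10% | 0.53 | 0.54 | 0.79 |
| 15% | 0.996 | 0.97 | >0.99 |

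A pooled percentage is a weighted average of the panel percentages. If it reaches 10%, at least one panel has reached 10%. The either-panel rule therefore admits everything the pooled rule admits.

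**Step 4: what happens to an added domain.** With two rounds, the only subsequent round is Round 2. The feedback items are the Round 1 panel medians and the participant's own Round 1 rating, and neither exists for a domain first shown in Round 2. Box 4 still classifies it. IN on that single rating means it is presented in Step 3 as IN, with no vote unless objection is raised. OUT is unlikely for a domain that 10% volunteered, but it is arithmetically possible: 10% rating 7–9 is below the 15% limit, and the other 90% can supply more than 70% rating 1–3.

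**The case against.** The strongest reply has four parts.

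- **The article does not say pooled.** It says respondents. It analyses scores by panel and mentions weighting for uneven panels. This stands: dilution follows from one reading, though the plainest one. Neither the panel analysis nor the weighting is tied to this rule, so the denominator remains unstated.
- **Free text is a backstop.** The long list also draws on reviews and at least 20 interviews sampled for variation across continents, conditions and interest holder groups. The executive group and the patient/public advisory group then review it at least twice, including for comprehensiveness. This stands too: few late additions may be entirely proper, and rarity alone is no defect.
- **The single rating matters little.** NO CONSENSUS domains already go to a vote, objection can reopen any status, and a third round is possible. This stands in part. The gap is confined to IN or OUT reached on one rating with no third round and no objection.
- **A lower bar has a price.** All questions are mandatory and all items are kept between rounds, so each addition adds burden. This stands, and it counts against a very low count.

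A reader might infer that the rule can hardly ever add a domain. The article does not support this. At 300 respondents the chance is 0.0003 at a 5% mention rate, but about even at 10% and 0.996 at 15%, and the true rate is unknown. A reader might also infer that the bar gets stricter as recruitment succeeds. The headcount rises but the percentage does not. What raises the bar for a panel is uneven growth of the other one.

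**Conclusion.** The point holds in a limited form, as an inexpensive improvement rather than a flaw that undermines the study.

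The 10% rule lacks a denominator. If pooled, it doubles to 20% of the panel for a domain raised by one of two equal panels, and rises to 30% or 40% if that panel makes up a third or a quarter of respondents. With 150 patients among 300, and 10% of patients naming a domain no professional names, the chance of entry is 0.0002, against 0.54 under a within-panel 10% rule. This sits badly with the purpose of separating the panels. The result rests on the pooled reading, on a domain raised in one panel only, and on assumed mention rates. How often domains would be added overall cannot be settled from the article.

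The single-rating point is separate and needs no assumed rate. It holds whenever a domain is added and no third round is run. It does not stop a domain from entering; it leaves the status of one that has entered resting on a non-iterated score.

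**What to change.** In Step 2, Data collection, state that a new in-scope domain is added to Round 2 if at least 10% of respondents in either panel suggest it, or a lower pre-specified count within a panel. The count should be made after synonymous suggestions are grouped. If more than two panels are formed, say which ones the rule applies to. The choice between 10% and a lower count is a judgement that the article's figures do not settle.

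In Step 3, state that any domain first rated in Round 2 goes to the vote, with its ratings shown by panel, whatever its Box 4 status.

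Both sentences should be settled before the Round 1 free text is read, because that text decides what Round 2 contains. The cost is the work of grouping suggestions and a few more items in Round 2 and in the Step 3 vote. That number cannot be calculated from the article.
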